### Implementation

After assigning the GPs and training was given to the MISS group, patients were enrolled by screening the source population (see participants). The general practice team gave entrance to data on the source population, the source population was given the inclusion criteria through a screening questionnaire. The research assistance team was responsible for the final recruitment. They gave information in a phone survey and asked the patient informed consent to participate.

### Blinding

Patients were kept unaware that two different interventions were studied; both groups were given exactly the same information and questionnaires. The patients, as well as the external interviewers who carried out the phone surveys, were told that the study was about stress and sick leave. Finally, the internal research assistance team responsible for the process of data collection knew that the study involved a training of half of the GPs; nevertheless the internal research team had no information on which GPs were allocated to what conditions.

### Statistical methods

First of all, baseline similarity between the MISS and usual care groups will be examined, and baseline characteristics of drop outs and completers will be compared. Cox regression analyses will be used to investigate the intervention effect, by analysing differences in outcome with survival analysis of the primary outcome measure between the MISS and usual care group. To correct for misclassification of patients and severity of complaints (inclusion is only by level of distress with sick leave), and as a consequence to avoid bias in the effect, baseline measures of psychological symptoms (by means of the 4DSQ [31] & PRIME-MD [32]), as well as medical records will be examined. Additionally, subgroup analysis can be done by level of severity of complaints.

Linear and logistic multilevel analyses will be used to investigate the intervention effect on all secondary outcome measures: rates of return to work, psychological symptoms, problem experience and coping style. Also, longitudinal multivariate analysis will be used to examine differences in improvement in all secondary outcome measures between the treatment groups. Analysis will be performed on an intention-to-treat basis and intra-class-correlation will be calculated to correct for possible clustering of observations. Levels included will be: repeated measures, patients and GPs. Subgroups for analysis will be modelled by the prognostic factors mentioned.

Costs will be measured and valued from a societal perspective. Mean direct and indirect medical costs (measured with the Tic-P[26]), costs of productivity loss due to sick leave (measured with the WHO HPQ[28]) and total costs will be compared between both groups. Confidence intervals around mean differences will be estimated with bootstrapping methods. With regard tot the primary outcome, sick leave, a cost benefit analysis will be performed, in which costs of productivity loss due to sick leave will be compared with direct en indirect medical costs.

A cost-effectiveness analysis will be performed to assess the incremental costs per unit improvement on the 4DSQ [18]. Bootstrapping methods will be used to estimate the confidence interval for the cost-effectiveness ratio and to a draw cost-effectiveness plane. Similarly, utility assessed with the EuroQol [29] will be used to estimates the incremental costs per Qualy gained in a cost-utility analysis.

As regards the prognostic measures, univariate analyses will be used to select relevant factors, with a focus on identifying prognostic factors for our primary outcome measure. Subsequently, Cox regression analyses and logistic regression analysis will be performed on these relevant factors.

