### Power & sample size

Proportions used to determine the sample size needed, were adopted from a related study completed in the occupational health care setting [13]. In that study, after a period of 3 months 79% in the intervention group versus 64% in the control group had fully returned to work. In order to detect a relevant difference in survival analysis on our primary outcome measure, nQuery Advisor [30] was used to calculate the sample size. With a power of 80% at a 0.05 level two-sided log-rank test for equality of survival curves between the MISS group proportion still on sick leave of 0.21 and a usual care group proportion of 0.36 at the given time of 3 months, the sample size needed in each group was 126 (with a constant hazard ratio of 1.528). Taking into account an intracluster correlation coefficient (ICC) of .025 (clustering effect in our groups is not presumed to be large) for randomisation at GP level and 7 patients per cluster (GP), a total of 290 patients are needed. Assuming a dropout rate of 30% (approximately 10% at each follow up), inclusion of a total of 415 patients is necessary.

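### The plan does not secure an allowance for GP clustering in the primary Cox analysis, although GPs were randomised and the sample size allows for it

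*Protocol article*

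**What the plan says.** All references are to the Protocol article.

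- **Randomisation:** the GP is the unit, with 24 GPs allocated to MISS and 22 to usual care. The Abstract gives 433 patients.
- **Outcome measures, Sick leave:** the primary outcome is one duration per patient, from the first day of sick leave to lasting full return to work.
- **Power & sample size:** the log-rank calculation for this outcome is inflated for clustering: "Taking into account an intracluster correlation coefficient (ICC) of .025", with "7 patients per cluster (GP), a total of 290 patients are needed".
- **Statistical methods, first paragraph:** "Cox regression analyses will be used to investigate the intervention effect, by analysing differences in outcome with survival analysis of the primary outcome measure". No frailty, GP effect or cluster-robust variance is named.
- **Statistical methods, second paragraph:** it opens with "Linear and logistic multilevel analyses will be used to investigate the intervention effect on all secondary outcome measures" and goes on to longitudinal models for the same outcomes. It then commits to intention to treat and says that "intra-class-correlation will be calculated to correct for possible clustering of observations". The next sentence lists three levels: repeated measurements, patients and GPs.

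**The concern.** The section allots methods by outcome. Where it names a method that handles clustering, it names it for the secondary outcomes. The primary outcome gets a Cox regression with nothing said about GPs. An analyst could follow the text to the letter and report an ordinary Cox model, with standard errors that treat 433 patients as independent although only 46 units were randomised. For any positive ICC that interval would be too narrow, and the test would reject too often.

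This is the confirmatory comparison of a trial that hopes to inform a guideline. The design has already paid for clustering on this outcome through a larger sample, so the analysis should be certain to use that allowance.

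**Working it through.** **1. Reproduce the sample size.** Inputs from Power & sample size: "With a power of 80% at a 0.05 level two-sided log-rank test for equality of survival curves", and "MISS group proportion still on sick leave of 0.21 and a usual care group proportion of 0.36" at 3 months.

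- Hazard ratio = ln(0.21)/ln(0.36) = 1.528, as stated.
- Events (Freedman) = (1.960 + 0.842)² × [(1.528 + 1)/(1.528 − 1)]² = 179.9, so 180.
- Mean event proportion = 1 − (0.21 + 0.36)/2 = 0.715. Patients per group = 179.9/0.715/2 = 125.8, so 126, as stated.
- Design effect = 1 + (7 − 1) × 0.025 = 1.15. Total = 252 × 1.15 = 289.8, so 290, as stated.
- Dropout: 290/0.70 = 414.3, so 415, as stated.

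The plan therefore applies its clustering allowance to the primary outcome, and correctly so on its own inputs.

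**2. Does the text carry the allowance into the primary analysis?**

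| Feature of Statistical methods | Points to |
|---|---|
| Cox sentence names no GP term | Not secured |
| Multilevel models named for secondary outcomes only | Not secured |
| Clustering sentence stands among the secondary-outcome methods | Secondary outcomes only |
| Listed levels include repeated measurements, but the primary outcome is one duration per patient | Secondary outcomes only |
| Clustering sentence shares its clause with the intention-to-treat commitment and is not limited to secondary outcomes | Whole trial |
| GPs are among the listed levels | Compatible with either |

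Both readings are open. Even on the whole-trial reading, calculating an ICC is not in itself a correction to a hazard ratio or its standard error.

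**3. Size, if an ordinary Cox model were run.** With design effect DE = 1 + (m − 1) × ICC, the true two-sided error of a nominal 5% test is 2 × [1 − Φ(1.96/√DE)]. The correct interval is √DE times the naive one. Applying DE to the log hazard ratio is an approximation, the same one the plan makes for its log-rank calculation.

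| Patients per GP (m) | ICC | DE | √DE | Type I error |
|---|---|---|---|---|
| 7 (plan) | 0.025 (plan) | 1.150 | 1.072 | 6.8% |
| 433/46 = 9.41 | 0.025 (plan) | 1.210 | 1.100 | 7.5% |
| 9.41 | 0.01 (assumed) | 1.084 | 1.041 | 6.0% |
| 9.41 | 0.05 (assumed) | 1.421 | 1.192 | 10.0% |

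With ICC = 0 there is no inflation. The table assumes equal cluster sizes. An assumed coefficient of variation of 0.4 to 0.6 in cluster size, at 9.41 per GP and ICC 0.025, gives DE of 1.25 to 1.30 and an error of 7.9% to 8.5%.

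**4. Simulation check.** The set-up was a gamma GP frailty, 433 patients in 24 versus 22 GPs, 12 months of follow-up, 30% dropout and no treatment effect. With the frailty variance (0.044) set so that the ICC of still being on sick leave at 3 months is 0.025, an unadjusted Cox or log-rank test rejected in 8.7% to 9.6% of replicates across runs, so about 9%. With no clustering it rejected in 4.9%.

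The result exceeds the formula's because the ICC is fixed at 3 months while the frailty goes on acting on events up to 12 months. The document does not say at what time its ICC applies, so this calibration is an assumption. An error of 9.2% corresponds to a correct interval 1.960/1.685 = 1.16 times the naive one.

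**The case against.** The strongest reply is that the document does commit to a correction. The sentence containing "intra-class-correlation will be calculated to correct for possible clustering of observations" is not limited to secondary outcomes, whereas the sentences just before it are. It is also the only intention-to-treat commitment in the document. If its position confined it to the secondary outcomes, the primary analysis would have no such commitment either, which is implausible. GPs are a listed level, and the list may pool levels across analyses. This stands. A reader might infer that the primary analysis has no adjustment for clustering, and hence that its interval is too narrow and its type I error exceeds 5%. The text does not support that flat statement.

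A reader might also take the word *possible* to mean that the correction will be dropped if the estimated ICC is small. The document sets no threshold or preliminary test, so this too is only a possible reading.

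A further reply is that the choice between frailty and robust variance, and any small-sample correction, is detail for an analysis plan that is not shown. That is fair as to the choice of method. It does not remove the point. By allotting methods by outcome, the article itself leaves in doubt whether the primary model is covered at all.

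**Conclusion.** The point holds as an ambiguity in the one analysis where clustering matters most. The text permits an ordinary Cox model as the primary analysis of a cluster-randomised trial, and it names no correction suited to a hazard ratio. It does not establish that such a model will be used.

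The error rates are therefore conditional on an unadjusted model. At the plan's ICC they are about 6.8% to 7.5% by the design-effect formula, which assumes equal cluster sizes, and about 9% under the simulation's assumption on when the ICC applies. For assumed ICCs of 0.01 to 0.05 at 9.4 patients per GP, the formula gives 6.0% to 10.0%. The inflation is modest but avoidable. This should be fixed; it falls short of a demonstrated invalid test.

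**What to change.** Add one sentence to Statistical methods: the primary Cox model accounts for clustering by GP whatever the estimated ICC, by a shared GP frailty or by GP-clustered robust standard errors with a small-sample correction for 46 clusters. State that the same holds for any other Cox estimate of the intervention effect, for example if time to first return to work is analysed that way. Keep the existing multilevel wording for the secondary outcomes.

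The cost is an interval about 10% wider (formula, 9.4 per GP) to 16% wider (simulation) at ICC 0.025. The recruitment target does not change, because 290 analysed and 415 included already carry the design effect of 1.15. With 290 × 0.715 = 207 events, divided by 1.15, power is 80.1% on the Freedman calculation.

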### General Practice treatment of SMDs in patients on sick leave

Nearly every employee contacts the GP at the beginning of the sick leave. Most patients having SMDs are managed in primary care, and not referred to specialised secondary care. And despite the fact that mental health problems are common in primary care, GP's may still find it difficult to diagnose and treat them, unless they have a high index of suspicion [10]. Due to the collaborative nature of the doctor-patient relationship in general practice, many GPs may be overly cautious to attribute symptoms to a psychosocial cause. Another issue is an adequate differential diagnosis; many patients in primary care have symptoms related to anxiety, depression, somatization, or all three. In one out of five patients having a SMD there are prominent, although unrecognised symptoms of depression or anxiety, which are associated with a poor prognosis. A further pitfall is that GPs often tend to go along with the patient's request for rest and being left alone. Often GPs advise to go or stay on sick leave, to take rest, seek distraction and relaxation, instead of actively confront and cope with the difficulties. The distress of a lasting crisis combined with existing vulnerabilities may lead to prolonged disability and contribute to the development of serious mental disorders, e.g. depression or anxiety disorders. Earlier research revealed that about 20% of patients having a SMD stayed on sick leave for more than a whole year [11]. Cooperation between GPs and the occupational health care system seems to be in the best interest of all involved and also the preferred way to manage SMDs with sick leave.

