### Outcome measures

#### Sick leave

The primary outcome measure is defined as: duration of sick leave in calendar days from the first day of sick leave to full return to work, lasting at least 4 weeks without (partial or full) relapse. Variables of the rehabilitation process itself, like the time to first (partial or full) return to work, total days of sick leave in the whole year, and (partial or full) return to work rates after 2, 6 and 12 months, are secondary outcome measures. Sick leave in the past year is considered to be a prognostic factor for our primary outcome measure, as are job content data [21,22].

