### Data collection

At baseline, patients who entered the study were measured by a phone survey and received a questionnaire by mail. Follow-up measurements, again a phone survey followed by a questionnaire, were scheduled at 2, 6 and 12 months after baseline. All outcomes were measured at the level of the patient, except for the GP interventions and skills. These were reported by the GPs two months after baseline. Moreover, data on received health care were extracted from the medical records after the completion of the one year follow-up.

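### The return-to-work rates at 2, 6 and 12 months are sent to a logistic model with a patient level, which gives no usable odds ratio if return is one-way and may overstate the group difference if it is not

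*Protocol article*

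**What the plan says.** The Sick leave section under Outcome measures lists as secondary outcomes the "partial or full) return to work rates after 2, 6 and 12 months, are secondary outcome measures". The Data collection section has the follow-up phone surveys and questionnaires, which "were scheduled at 2, 6 and 12 months after baseline".

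The Statistical methods section states: "Linear and logistic multilevel analyses will be used to investigate the intervention effect on all secondary outcome measures: rates of return to work", followed by psychological symptoms, problem experience and coping style. It continues: "Also, longitudinal multivariate analysis will be used to examine differences in improvement in all secondary outcome measures between the treatment groups". After both sentences it fixes the structure: "Levels included will be: repeated measures, patients and GPs".

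The article does not say whether a return-to-work rate is work status at the visit or return achieved by then. It recognises relapse, because the primary outcome requires a return "lasting at least 4 weeks without (partial or full) relapse", but it gives no relapse rate.

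**The concern.** A random intercept for the patient describes stable differences between people, with each person's repeated values scattering around their own level. Symptom, problem and coping scores can behave like that. Return to work may not. If the rate counts patients who have returned by each time point, the only possible sequences over the three visits are 000, 001, 011 and 111. A patient-level logistic model fits such data ever more closely as the patient standard deviation (SD) grows, and the arm coefficient grows in proportion.

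If the rate is status at the visit, sequences can reverse and the model has a finite solution. Its odds ratio then compares two hypothetical patients with the same random effect, whereas the outcome as defined is a rate in each group. The two can differ widely when the patient SD is large.

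These rates are the sick-leave result that GPs and guideline writers will read most easily. An odds ratio several times larger than the rates imply, or one set by a convergence tolerance, would mislead them.

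**Working it through.** **The plan's own figures.** From the Power & sample size section, the hazard ratio is ln(0.21)/ln(0.36) = 1.528, as stated. Events by Freedman's formula are 7.849 × (2.528/0.528)² ≈ 180. Dividing by 1 − (0.21 + 0.36)/2 = 0.715 gives 252, or 126 per group. Then 252 × [1 + (7 − 1) × 0.025] = 289.8, rounded to 290, and 290/0.70 = 414.3, rounded to 415. All of these reproduce, and the present point does not touch them.

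**Inputs for the check.**
- Usual care, 36% still on sick leave at 3 months, and hazard ratio 1.528 (Power & sample size).
- Earlier research: "about 20% of patients having a SMD stayed on sick leave for more than a whole year" (Background).
- 433 patients, taken as 216.5 per arm.
- Assumed, because the documents do not give them: the shape of the curve, the relapse rate, and time counted from the start of sick leave.

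**Curves.** The Weibull curve through 0.36 at 3 months and 0.20 at 12 months has shape ln[ln(0.20)/ln(0.36)]/ln(4) = 0.328. The proportions returned at 2, 6 and 12 months are 59, 72 and 80% under usual care and 75, 86 and 91% under the intervention. The differences are 15, 14 and 11 points and the between-arm odds ratios 2.0, 2.3 and 2.7. The alternative is a constant hazard through 0.36 at 3 months.

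**Model.** logit P(returned) = time effect + β × arm + patient effect, with the patient effect normal with SD σ. It was fitted by maximum likelihood to the expected frequencies of the response sequences. The GP level was left out; its effect is checked at the end.

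**Reading 1: returned by each time (one-way), Weibull curve.**

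| σ | log-likelihood | arm odds ratio | ln(OR)/σ |
|---|---|---|---|
| 2 | −496.3 | 3.7 | 0.65 |
| 4 | −445.9 | 8.3 | 0.53 |
| 8 | −425.0 | 46 | 0.48 |
| 16 | −419.7 | about 1,600 | 0.46 |
| 32 | −419.2 | above 10⁶ | 0.46 |

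The likelihood never turns down. The last column shows why: the data fix only the ratio β/σ, at about 0.46, so the odds ratio behaves like exp(0.46σ) with σ unbounded. Under constant hazards the log-likelihood goes flat (−394.98 at σ = 8, −394.96 at 16 and 32) while the odds ratio runs from 36 to about 1,160 to above 10⁶.

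**Reading 2: status at the visit, with an assumed share of returned patients off work at each visit.**

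| Off work | Weibull: fitted OR | Weibull: between-arm ORs | Constant hazard: fitted OR | Constant hazard: between-arm ORs |
|---|---|---|---|---|
| 2% | 11.6 | 2.0–2.4 | 2.7 | 1.7–2.6 |
| 5% | 4.8 | 1.9–2.1 | 2.05 | 1.3–2.1 |
| 10% | 2.9 | 1.8 | 1.7 | 1.15–1.7 |

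Modelling relapse as a move between visits instead changes little: 11.5, 5.2 and 3.2 on the Weibull curve for 2, 5 and 10%.

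**One time point, GP as the only cluster level.** Applying the plan's ICC of 0.025 on the logistic scale gives a GP variance of 0.025/0.975 × 3.29 = 0.084. The conditional log odds ratio exceeds the population-averaged one by a factor of √(1 + 0.346 × 0.084) = 1.014, or about 1.4%. The problem disappears.

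**The case against.** The tempting stronger reading is that return to work is nearly absorbing, so the planned odds ratio must be infinite or grossly inflated. The documents do not support that. They speak of rates *after* each time, tie those times to the surveys, recognise relapse, count partial return, and admit patients who are only partially on leave. Status at the visit is therefore a natural reading, and under it the estimate is finite.

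The large excess on the Weibull curve also rests on joining two outside samples. One reports full return in an occupational setting, the other long-term absence. Neither allows for up to three months of leave before baseline. Under constant hazards the excess is small or absent. On the other side, a constant hazard implies 0.36⁴ = 1.7% still off at 12 months, which sits badly with the article's figure of about 20%. Neither curve is established.

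The first sentence could also mean one model per time point, with patients nested in GPs. That would be harmless. However, the longitudinal analysis explicitly covers all secondary outcomes and the list of levels follows both sentences, so a patient-level logistic model still reaches this outcome.

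Finally, a patient-conditional odds ratio is a different quantity rather than an error, and group rates can be derived from a finite fit. That is true, but the article does not plan the derivation, and on the one-way reading there is no finite fit to derive from.

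An article may leave detail to a fuller plan. This point concerns the method the article does state.

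**Conclusion.** The point holds in a conditional form. The stated model is a poor match for the return-to-work rates under either meaning of the rate, but how badly depends on facts the documents do not give.

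- *Returned by*: there is no usable finite estimate on either curve examined, and the odds ratio passes 1,000 by a patient SD of 16.
- *Status at the visit*: the estimate is finite. With 2 to 10% of returned patients off work at a visit, it is about 12 down to 3 against about 2 on the Weibull curve. Under constant hazards there is little or no excess at 5% or more.

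The relapse shares and both curves are assumptions. The matter is worth correcting because the article names the model and the remedy is simple, but it concerns a secondary outcome only.

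**What to change.** In the Statistical methods section:
- Exempt return-to-work rates from the patient-level logistic model, in both the multilevel and the longitudinal analysis.
- State whether the rate is work status at the visit or return achieved by then.
- Analyse each time point separately with GP as the only cluster level (GP-level logistic model or GEE clustered on GP). Report each arm's rate and the population-averaged difference with a GP-clustered interval.
- Use proportions read from survival curves only if the rate is defined as returned-by; for visit status they would discard relapse.
- Keep the three-level model for symptom, problem and coping scores.

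This costs a sentence or two and needs no new data. The price is that there is no single pooled odds ratio across the three time points.

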### Intervention at the level of general practitioners

In order to use the intervention, additional training in the MISS was given to intervention GPs by one of the authors (BT), and an occupational physician. This training existed of two times 3,5 hours and 2 times follow-up of 2 hours (total of 11 hours). Skills needed for successful treatment were accentuated. The participating GPs own experiences were evaluated; they were expected to provide case histories and to practice with the different parts of the intervention during the training. Screening of eligible patients started after the MISS group got the second training. When a patient had signed the informed consent (about four weeks after oral informed consent in the telephonic baseline measure), the GP was informed of the participation. Actual application of the elements of the MISS and steps in usual care are measured with a questionnaire.

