#### Economic evaluation

Cost effectiveness will be evaluated from societal perspective (that is, irrespective of who is paying for the costs to gain an effect) by using the Tic-P [26]. The employers perspective (expenditures for the employer) is represented by the HPQ [27,28]. The EuroQol [29] measures general health state, and as a result quality of life status, that can be compared with a wide range of conditions in health care.

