### Randomisation

Randomisation took place at the level of GPs, after each of the four recruitment moments and after the GPs signed informed consent. Because balance between groups in size and characteristics was presumed all four times GPs were randomised, no blocking or stratification was used. We developed the following procedure to conceal allocation. The names of the GP's (and dummy in an uneven group) were put on a list of which the order was subsequently randomised by one person ([name]). Another person (BT) independently drew up a randomised list of codes (1 = MISS group and 2 = control group) with an equal number of '1' and '2' codes up to the number of GPs being randomised. Finally, these two lists were brought together and the first GP on the list was allocated to the group indicated by the first code; and so on. As a result, 24 GPs were allocated to the intervention (MISS) group and 22 GPs were allocated to the control (usual care) group.

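### The listed costs leave out the MISS training, and the planned confidence interval for the cost-effectiveness ratio cannot be interpreted if the effect difference is near zero

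*Protocol article*

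**What the plan says.** Under Statistical methods the article states: "Costs will be measured and valued from a societal perspective". The Economic evaluation section explains that perspective as "irrespective of who is paying for the costs to gain an effect". The components compared between arms are then named with their instruments, and the list closes with their sum: "Mean direct and indirect medical costs (measured with the Tic-P[26]), costs of productivity loss due to sick leave (measured with the WHO HPQ[28]) and total". The cost-benefit analysis sets lost productivity against medical costs.

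On uncertainty, "Confidence intervals around mean differences will be estimated with bootstrapping methods". For the cost-effectiveness analysis on the 4DSQ, "Bootstrapping methods will be used to estimate the confidence interval for the cost-effectiveness ratio", and a cost-effectiveness plane is to be drawn. The cost-utility analysis is to proceed in a similar way.

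The training is described under Intervention at the level of general practitioners: "This training existed of two times 3,5 hours and 2 times follow-up of 2 hours (total of 11 hours"). It was given by one of the authors and an occupational physician. Under Randomisation, "24 GPs were allocated to the intervention (MISS) group and 22 GPs were allocated to the control (usual care) group".

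**The concern.** Training is what was randomised: one group of GPs received it and the other did not. It is therefore the resource that most clearly separates the arms, and a perspective that counts costs whoever pays should include it. It appears in neither the component list nor the two sides of the cost-benefit analysis. Leaving out a cost that only one arm bears shifts the incremental cost in a known direction, here towards MISS.

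The second issue is the form of the inference. A ratio of cost difference to effect difference has no stable meaning when the denominator may be zero or change sign. A negative ratio can mean that MISS is cheaper and better, or dearer and worse. A positive ratio can mean dearer and better, or cheaper and worse. An interval that orders ratios by size mixes these cases.

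A small effect difference is realistic here. Under Intervention at the level of the patients, GPs were not required to apply MISS and patients were not required to visit. The Discussion presents the results as a possible contribution to guidelines, where a cost claim would carry weight.

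**Working it through.** **1. Training load.** Inputs: session lengths (Intervention at the level of general practitioners); 24 MISS and 22 control GPs (Randomisation); 433 patients and 46 GPs (Abstract); 7 patients per GP (Power & sample size).

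- Hours per GP: 2 × 3.5 + 2 × 2 = 11. This reproduces the article's total.
- GP hours in the MISS arm: 24 × 11 = 264. Control arm: 0.
- MISS patients are not reported by arm. Pro rata: 433 × 24/46 ≈ 226.
- Hours per MISS patient, all training charged to trial patients: 264/226 ≈ 1.2. With the planned 7 patients per GP: 11/7 ≈ 1.6.
- For scale, MISS is described as at most three consultations of up to 20 minutes: 3 × 20 = 60 minutes per patient.

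Trainer time comes on top. The article does not say how many courses were run. If both trainers attended every session, one course gives 2 × 11 = 22 trainer hours. One course for each of the four recruitment rounds gives 4 × 22 = 88.

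**2. In euros.** No unit cost is given. At an assumed 50 to 150 euro per GP hour, with all training charged to trial patients:

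- low: 11 × 50/9.41 ≈ 58 euro per MISS patient (433/46 ≈ 9.41 patients per GP);
- high: 11 × 150/7 ≈ 236 euro per MISS patient.

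This range is illustrative. It excludes trainer time, and it falls if the training is spread over later patients.

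**3. Could the listed instruments pick the training up?** Data collection says that outcomes were measured on patients, apart from GP interventions and skills. Blinding says that patients were not told that two approaches were being compared. Patients therefore cannot report their GP's course hours, and the HPQ is used for productivity lost through sick leave.

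**4. The ratio interval.** The check used 200,000 draws of an effect difference and a cost difference, each normal, independent and in units of its own standard error. The cost difference was set at −1 (MISS somewhat cheaper). These settings are assumptions; the article gives no figures for the economic outcomes.

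| Effect difference (SE units) | Replicates with negative effect | 2.5 to 97.5 percentile of the ratio |
|---|---|---|
| 0.5 | 30.9% | −17.02 to 15.94 |
| 1 | 15.8% | −12.31 to 10.31 |
| 2 | 2.3% | −3.82 to 1.16 |
| 3 | 0.1% | −1.50 to 0.37 |

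At an effect difference of 1, negative ratios combine 70.9% of replicates in the south-east quadrant (cheaper and better) with 2.5% in the north-west (dearer and worse). The positive ratios, 100 − 70.9 − 2.5 = 26.6% of replicates, combine the north-east and south-west quadrants. At 3 the difficulty has almost gone.

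Incremental net benefit, λ × (effect difference) − (cost difference), involves no division. Its interval is well defined in every row, for any value λ placed on a unit of effect.

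**The case against.** **Training.** The article names two instruments and then a total; it never says that nothing else enters the total. Its definition of the perspective is wide enough to cover intervention costs, and an article may leave detailed costing to a fuller plan. This stands to the extent that the bias is conditional: it arises if the analysis follows the list. It does not remove the point, because the list is itemised by instrument and both sides of the cost-benefit analysis are fixed without training. It is also fair that training is a one-off investment in GP skills, so charging all of it to trial patients overstates its long-run cost per patient. That is a reason for a sensitivity analysis, not for a zero.

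**Ratio interval.** The planned plane displays the spread over quadrants, and with a clear effect the interval is usable. Both statements are true. But the plane does not change what the interval reports, and the method has to be chosen before it is known which case applies.

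**Clustering.** A reader might infer that the bootstrap ignores GP clusters and that its intervals are therefore too narrow. The document does not support this. It does not state the resampling unit, and a correction for clustering with a GP level stands in the same section. That correction is in the paragraph on the non-cost secondary outcomes, so the matter is open either way. Nor can the consequence be sized: the ICC of 0.025 is a sample-size assumption for return to work, and none is given for costs. If that value did apply and patients were resampled, the standard error would be understated by a factor of √1.15 ≈ 1.07 (7 patients per GP) to √1.21 ≈ 1.10 (9.4 per GP).

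**Conclusion.** The point holds in two parts, both confined to the secondary economic evaluation.

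- **Training cost.** If costs are analysed as listed, incremental cost is understated for MISS by the cost of 264 GP hours plus trainer time. The direction is certain on that condition. The figure of about 1.2 hours per MISS patient rests on a pro rata split of patients and on charging all training to them. The size in euros, and whether it would change any conclusion, cannot be derived from the document.
- **Ratio interval.** The stated method gives an interval without a clear reading if the effect difference is small relative to its standard error. Whether that will happen is unknown, but optional delivery of MISS makes it plausible.

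The document does not show that the economic results will favour MISS regardless, or that their uncertainty will necessarily be misstated.

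**What to change.** 1. Add GP training hours and trainer hours, each with a stated unit cost, to MISS-arm costs. Do this both in total costs and in the cost-benefit analysis. In the main analysis, spread them over the trial's MISS patients; in one sensitivity analysis, spread them over a longer period of use.
2. Report incremental net benefit over a range of values of λ, with an acceptability curve, beside the planned plane. Let this replace the ratio interval or stand as the main inference over it, in both the 4DSQ and the EuroQol analyses.
3. As a clarification, state whether the bootstrap resamples GPs within arm and then patients.

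No new patient data are needed. GP hours are in the article; trainer hours need the number of courses run. The price is extra analysis work and a less favourable cost figure for MISS.
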